## Data collection and management

### Plans for assessment and collection of outcomes {18a}

Trial data collected includes general assessments (i.e. vital signs, pregnancy testing), laboratory assessments using blood collection samples and diabetes-specific assessments, including records obtained from each participant’s glucose diary and records of insulin use. Trial data at each study visit will be collected by study site personnel and recorded using an electronic case report form (eCRF). The relevant personnel have received training on how to use this system. Each data point entered into the eCRF will be verifiable against an original source record, such as the medical record or other participant notes.

### Plans to promote participant retention and complete follow-up {18b}

Participation in the trial provides the benefit of intensive diabetes management and thus will ideally encourage retention and completion of the trial. In addition to frequent study visits, participants will also be regularly contacted by the study team outside of the normal visit schedule via scheduled telephone calls, which will take place during the treatment and follow-up period.

Phone contacts are scheduled so that participants have contact with the study team via visit or call approximately every 2–3 weeks during the first 24 weeks, every 3–5 weeks during weeks 25–48 and every 6–8 weeks during the follow-up period.

Participants who prematurely exit the study will still be encouraged to participate in regular follow-up visits, ensuring data will continue to be collected. If the participant does not consent to follow-up visits, they should complete an end-of-study visit, which will include general, laboratory and diabetes-specific assessments as per the schedule of assessments.

### Data management {19}

All trial data will be entered onto the eCRF. Each data point entered will be verifiable against an original source record, such as the medical record or other participant notes. The eCRF contains checks for data values.

Data management will be performed using Viedoc Electronic Data Capture (EDC) system to collect, store and maintain the study research data. Viedoc EDC system is a 21 CFR Part 11 compliant database that is web/cloud based and has automatic hourly data backups. On study completion, the data will be downloaded and securely stored on the sponsor’s server in compliance with the data management plan, which conforms to electronic data standards.

Viedoc EDC system enables multisite users to contribute via the internet to a secure database and allows the study coordinator to oversee all data entries. Access to the trial database is password protected and will be restricted to certain study team members, with different levels of access assigned by the study coordinator.

Data will be stored for at least 15 years in compliance with local guidelines (Australian code for responsible conduct of research, NHMRC, 2018). In addition, data obtained from minors will be stored for 7 years after a child’s 18th birthday, or 15 years after the end of the study—whichever date is latest. If trial sites have a longer retention period, this will be observed for data from that site. After this time, the participants identifying information at the institution will be permanently deleted from the computer system and any hard copies will be destroyed. If extended or unspecified consent is obtained for future research, then data may be kept indefinitely.

### Confidentiality {27}

Any identifying participant information obtained for the study will remain confidential. No personal information that can be linked to a participant, such as their name and address, will leave the clinic sites. Only the researchers at the clinic site will have access to the code that links a participant to their data, and all information will be coded before it leaves the clinic.

Information about participants may be obtained from their health records held at the clinic site and other health services, for the purpose of the research. By signing the consent form, participants agree to the study team accessing health records if they are relevant for the study.

In any publication and/or presentation, information will be provided in a grouped or de-identified format so that participants cannot be identified.

### Plans for collection, laboratory evaluation and storage of biological specimens for genetic or molecular analysis in this trial/future use {33}

Genomics data will be stored in a repository at the St Vincent’s Institute of Medical Research in compliance with SVI’s data management plan. Before genomics data can be accessed and used for future research studies, approval from the hospital’s Human Research Ethics Committee will be obtained. Access to the databank will be restricted to certain study team members and access assigned by the data custodian (Coordinating Principal Investigator).

Also see item 26b.

## Statistical methods

### Statistical methods for primary and secondary outcomes {20a}

All analyses will be performed using either SPSS 22 (IBM Corp. Armonk, NY, USA) or Stata15 (StataCorp LP, College Station, TX, USA). An experienced biostatistician will oversee data collection and data analysis. Primary analysis will be performed based on intention to treat (ITT) with sensitivity analysis as per protocol to confirm the robustness of the findings. In case of participants missing the follow-up assessment, appropriate imputation techniques will be employed in consultation with the study statistician. All continuous data will be tested for normality prior to the data analysis and appropriate transformations will be applied for skewed data. The C-peptide levels will be log transformed using log(C-peptide+1) as appropriate. ANOVA analysis will be used to examine the change in primary outcome between groups.

The baseline differences between study arms will be examined using *T*-test for continuous normally distributed data, while the Wilcoxon rank-sum test will be used for skewed or ordinal data and either chi-2 or Fisher’s exact for categorical data. Multilevel mixed effect model will be constructed to examine the impact of intervention on longitudinal changes in primary outcome while controlling for potential confounders including gender, baseline age and C-peptide level.

Secondary and exploratory outcomes will be assessed using either ANOVA or Fisher’s exact test for continuous and categorical data respectively. Multilevel mixed effect regression analysis will be used to examine longitudinal changes while controlling for potential confounders, either identified during the analysis or those of clinical relevance. The per-protocol analysis will be performed, including only those who received at least 50% of the treatment in order to confirm the robustness of the ITT results. Logistic regression will be used to examine the risk of developing adverse events (AE) or SAEs. Any deviations from the original data analysis plan will be documented and reported as appropriate.

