### Objectives {7}

The primary objective is to assess whether baricitinib can reduce the loss of plasma C-peptide in patients with new onset T1D after 48 weeks of treatment. The study has several secondary objectives. Firstly, to assess the efficacy of baricitinib at additional timepoints on mitigating the loss of plasma C-peptide; secondly, to assess the effect of baricitinib on secondary clinical outcomes including insulin dose, haemoglobin A1c (HbA1c) and estimated C-peptide (CP_EST_) [29], a surrogate measure of beta cell function; and finally, to assess the safety and tolerability of baricitinib in participants with T1D. Additional exploratory objectives aim to establish the immune mechanism by which baricitinib impacts T1D and evaluate the impact of baricitinib on T1D-associated immune responses.

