### Outcomes {12}

The primary endpoint of the study is plasma C-peptide area under the curve (AUC) over 2 h following a mixed meal tolerance test (MMTT) at 48 weeks.

The secondary endpoints of the study are:Change from baseline in 2-h MMTT-stimulated C-peptide AUC at weeks 12, 24, 72 and 96Change from baseline in mean daily insulin use over 7 consecutive days during the 2 weeks prior to the assessment at weeks 12, 24, 48, 72 and 96Change from baseline in glycosylated haemoglobin (HbA1c) levels at weeks 12, 24, 48, 72 and 96Number of participants with responder status at weeks 12, 24, 48, 72 and 96Change in estimated C-peptide (CP_EST_) [29] from baseline at weeks 12, 24, 48, 72 and 96Continuous glucose monitoring (CGM) at baseline, 12, 24, 48 and 96 weeksFrequency and severity of all adverse events.

The following mechanistic endpoints will be assessed at baseline, 12, 24, 48 and 96 weeksAnalysis of total and antigen-specific T cells, including tetramer analysisTreg analysis

The following mechanistic endpoints will be assessed at baseline, 24 and 96 weeksAssessment of IFNγ, IL-21 and IL-7 induced STAT1, STAT3 and STAT5 phosphorylation respectively in whole bloodPBMC analysis using flow cytometry, including markers for lineage, activation, exhaustion and cytokine signalling10x Chromium single cell sequencing

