### Sample size {14}

The sample size of 83 participants was selected based on estimates of 2-h AUC mean C-peptide obtained from prior studies and using standard power calculations for comparison of treated and placebo groups [30, 31].

Using standard equations for comparison of two means, a sample size of 50 baricitinib treated and 25 placebo treated participants with complete data is needed to provide 80% power to detect 45% increase in mean log(C-peptide+1) (0.306 vs. 0.445, sd of 0.2), in the treated group using a two-sample *T*-test at 0.05 level of significance (two-sided). With the expected 10% dropout rate, the number of participants recruited into the study will be increased to 83 (55 and 28 in the intervention and control arms respectively). Should the number of drop-outs exceed 10%, additional participants may be recruited.

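### The primary outcome is assigned an ANOVA of change with no covariate, while the endpoint and power concern the week-48 level; no single baseline-adjusted analysis is named as primary

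*Protocol article*

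**What the plan says.** All references are to the protocol article.

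- **Objective.** Objectives {7} sets out to "assess whether baricitinib can reduce the loss of plasma C-peptide in patients with new onset T1D after 48 weeks of treatment".
- **Endpoint.** Outcomes {12} gives the primary endpoint as "plasma C-peptide area under the curve (AUC) over 2 h following a mixed meal tolerance test (MMTT) at 48 weeks", which is a level. The same section words the secondary C-peptide endpoints at the other weeks explicitly as changes from baseline.
- **Power.** Sample size {14} uses a two-sample t-test with 50 and 25 completers to "detect 45% increase in mean log(C-peptide+1) (0.306 vs. 0.445, sd of 0.2", at two-sided 0.05 and 80% power. These are levels on the log scale.
- **Analysis.** Statistical methods {20a} states: "ANOVA analysis will be used to examine the change in primary outcome between groups". No covariate is attached to that sentence. The next paragraph adds: "Multilevel mixed effect model will be constructed to examine the impact of intervention on longitudinal changes in primary outcome". The covariates listed for this model are sex, age at baseline and C-peptide.
- **Secondary outcomes.** "Secondary and exploratory outcomes will be assessed using either ANOVA" for continuous measures, with a further mixed model whose covariates may be chosen during the analysis.
- **Baseline data.** Participant timeline {13} schedules a mixed meal test at the second screening visit, so baseline C-peptide AUC is available. Sequence generation {16a} stratifies by age below 21 versus 21 and over.

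**The concern.** Three sections describe the primary comparison, and they do not describe the same variable. The endpoint and the power calculation use the week-48 value. The analysis sentence, read naturally, uses a change. The planning SD of 0.2 belongs to the level, and a change score has a different SD except in a special case.

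The analysis sentence also leaves out baseline C-peptide, which is measured and which the protocol itself treats as worth adjusting for in the mixed model. With about 25 evaluable placebo participants, a chance difference at baseline can be large relative to the effect sought, and an unadjusted comparison carries part of it into the estimate.

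Because neither analysis is called primary, at least three results could be presented as the main one: unadjusted level, unadjusted change, or adjusted mixed model. Unless the choice is fixed beforehand, it could be made after seeing the data.

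**Working it through.** **Inputs from the protocol (Sample size {14}):** difference 0.445 − 0.306 = 0.139 on log(C-peptide+1); SD 0.2; 50 and 25 completers; two-sided 0.05.

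**Assumed, not in the protocol:** correlation r between baseline and week-48 values, shown at 0.3, 0.5 and 0.7; equal SDs (0.2) at both times.

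**1. The plan's own figure.** The standard error is 0.2 × √(1/50 + 1/25) = 0.0490, so the non-centrality is 0.139 / 0.0490 = 2.84. The non-central t on 73 degrees of freedom gives 79.95% power, and the normal approximation gives 81.0%. Dropout: 75 / 0.9 = 83.3. The stated 80% reproduces for an unadjusted comparison of the week-48 level.

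**2. The alternatives.**

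- SD of a change score: 0.2 × √(2(1 − r)).
- Residual SD after adjustment for baseline: 0.2 × √(1 − r²).

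| | r = 0.3 | r = 0.5 | r = 0.7 |
|---|---|---|---|
| SD, level | 0.200 | 0.200 | 0.200 |
| SD, change | 0.237 | 0.200 | 0.155 |
| SD, ANCOVA | 0.191 | 0.173 | 0.143 |
| Power, level | 80% | 80% | 80% |
| Power, change | 66% | 80% | 95% |
| Power, ANCOVA (two covariates, 71 df) | 83% | 90% | 97% |
| Completers for 80%, change (normal approx.) | 105 | 75 | 45 |
| Completers for 80%, ANCOVA (normal approx.) | 69 | 57 | 39 |

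The level analysis needs 75 completers at any r.

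**3. Efficiency of ANCOVA.**

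- Against the level: 1/(1 − r²) = 1.10, 1.33, 1.96, a gain of 10%, 33%, 96%.
- Against a change score: 2(1 − r)/(1 − r²) = 2/(1 + r) = 1.54, 1.33, 1.18, a gain of 54%, 33%, 18%.

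**4. Cost of the covariates.** At r = 0, with two covariates, ANCOVA power is 79.92% against 79.95%, so the degrees of freedom spent are negligible.

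**5. Chance imbalance.** The level and change estimates differ by exactly the observed baseline difference. Its standard error is also 0.0490, which is 0.0490 / 0.139 = 35% of the planned effect. Given a baseline difference b, the level estimate is shifted by r × b and the change estimate by −(1 − r) × b. At r = 0.5 and b equal to one standard error, each moves by 0.0245, or 18% of the planned effect, in opposite directions. Adjustment for baseline removes this linear dependence.

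**6. Sensitivity to equal SDs.** With baseline SD s, the change score has the planned SD of 0.2 when r = s/0.4. For s = 0.16 that is r = 0.40; for s = 0.25 it is r = 0.625. At r = 0.5, change-score power is then 86% and 69% respectively, while ANCOVA stays at 90%.

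**The case against.** **The wording may be loose.** Change between groups may simply mean the difference between arms in the week-48 value. Outcomes {12} writes change from baseline in full when it means that. On this reading the ANOVA of two arms is the powered t-test, and no mismatch remains. This is a fair reading. It does not settle what the text means, and it leaves the missing covariate and the unnamed primary analysis untouched.

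**An adjusted model is already planned.** The protocol does include a mixed model for the primary outcome with baseline C-peptide among its covariates, and mixed models for the secondary outcomes. It would be wrong to say that baseline is ignored throughout. But the model is introduced as an addition, and the text does not rank it against the ANOVA.

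**An unadjusted comparison is valid.** In a randomised trial it is unbiased with correct type I error, and the sample size reproduces. That stands: this is a matter of precision and clarity. Model detail may sit in a statistical analysis plan that is not shown, but the article does state a method for the primary outcome, and that statement can be judged.

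**Two stronger readings are not supported.** A reader might infer that level and change target different estimands. On one scale and under randomisation, the expected baseline difference is zero, so the expected contrast is identical; only the variable and its variance differ. A reader might also infer that the trial is underpowered. With equal SDs, power falls below 80% only if a change score is really meant and r is below 0.5. The protocol gives no r, and above 0.5 a change score exceeds the plan.

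**Conclusion.** The point holds as a correctable weakness in how the primary analysis is specified. The endpoint and power sections use the week-48 level, the analysis sentence refers to change without a covariate, and an adjusted model stands beside it with neither designated as primary.

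Under the assumed range of r from 0.3 to 0.7 with equal SDs, ANCOVA beats both unadjusted readings. Against the level it adds roughly 4 to 18 percentage points of power, the gain growing with r. Against a change score it adds roughly 18 points at r = 0.3, 10 at r = 0.5 and 2 at r = 0.7. The exact size cannot be taken from the protocol because r and the baseline SD are not given. ANCOVA's advantage does not depend on equal SDs, apart from the negligible cost in degrees of freedom. Validity and the planned sample size are not in question.

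**What to change.** Before unblinding, replace the ANOVA sentence in Statistical methods {20a} with one named primary analysis, for example:

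*The primary analysis compares log(C-peptide AUC+1) at week 48 between arms by ANCOVA, adjusted for baseline log(C-peptide AUC+1) and age stratum (<21, ≥21 years).*

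The week-48 treatment contrast from the mixed model, with the same adjustment, would serve equally well if named instead. Whichever is not chosen becomes supportive. Keep the log base as used in the power calculation; the article does not state it.

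Analyse continuous secondary outcomes with their own baseline value as a covariate in place of plain ANOVA. Align Outcomes {12}, Sample size {14} and Statistical methods {20a} on the same variable and scale.

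The cost is wording in the protocol and analysis plan. The covariates are already collected, no extra participants are needed, and the recruitment target of 83 can stay, since its 80% power is conservative for the adjusted analysis. Trial status reports about 80 participants already randomised, so the analysis is the practical place left to gain precision.

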### Trial design {8}

The study is an investigator-initiated, randomized, two-arm (2:1, baricitinib to placebo), multicentre, double-blind, superiority, phase 2 clinical trial. The participants will be randomly assigned, in a 2:1 ratio, to either baricitinib for 48 weeks or placebo for 48 weeks and therefore will be followed for 96 weeks from the start of treatment.

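### Ordinary logistic regression for adverse events gives no finite odds ratio when an arm is empty or saturated, which at 55 versus 28 is likely for uncommon events; a small addition would cover this

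*Protocol article*

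**What the plan says.** The section on statistical methods for primary and secondary outcomes {20a} has one sentence specific to adverse events: "Logistic regression will be used to examine the risk of developing adverse events (AE) or SAEs". It names no penalised or exact form and gives no rule for an arm without events. The same section assigns Fisher's exact test to categorical secondary and exploratory outcomes in general, and does not say which method takes precedence for AEs.

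The Outcomes section {12} makes the frequency and the severity of adverse events a secondary endpoint, and the Objectives section {7} lists safety and tolerability among the secondary aims. Participants are "randomly assigned, in a 2:1 ratio, to either baricitinib for 48 weeks or placebo for 48 weeks", and the Sample size section {14} sets the arms at "55 and 28 in the intervention and control arms respectively". No expected AE or SAE rate is given anywhere.

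The Interim analyses section {21b} describes listings, tables and plots of safety results, including AE incidence. The section on adverse event reporting {22} has severity graded and AEs reviewed by treatment group.

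**The concern.** Maximum-likelihood logistic regression with treatment as the covariate needs, in each arm, at least one participant with the event and one without. If either is missing, the odds ratio is zero, infinite or undefined. Software then typically prints a very large coefficient with a meaningless standard error. The smaller arm has 28 participants, so an empty placebo cell is easy to get when events are uncommon.

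The events that the protocol singles out for safety committee review, such as gastrointestinal perforation, venous thromboembolism and serious opportunistic infection, are of the kind for which no placebo events would be unsurprising. Some events on baricitinib and none on placebo is also the pattern for which a reader most wants an effect size with an interval, and the AE-specific method would give neither.

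A second, smaller issue is that a per-participant yes/no model does not use repeat events, time at risk or grade, although the endpoint covers frequency and severity over 96 weeks.

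**Working it through.** **Inputs from the article.** Arms of 55 and 28 as randomised, or 50 and 25 with complete data (Sample size {14}). Event rates are not given, so every rate below is an assumption, shown over a range.

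**The plan's own figure.** The article states that "a sample size of 50 baricitinib treated and 25 placebo treated participants with complete data is needed" for means of 0.306 and 0.445, SD 0.2, two-sided 5% and 80% power.
- Placebo n = (1 + 1/2) × (1.960 + 0.842)² × 0.2² / 0.139² = 24.4, rounded up to 25, with 50 on baricitinib. This reproduces.
- Power at 25 and 50 is 0.800 by the noncentral t distribution.
- For 10% dropout, 75 × 1.10 = 82.5, rounded up to 83, as stated. Dividing gives 75/0.90 = 83.3, rounded up to 84. The difference of one participant has no bearing here.

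**Probability of no finite odds ratio.** With event probabilities p0 (placebo) and p1 (baricitinib), the estimate is finite only if neither arm is empty or saturated:

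P(not finite) = 1 − [1 − (1 − p0)^28 − p0^28] × [1 − (1 − p1)^55 − p1^55]

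Example at 2% in both arms: 0.98^28 = 0.568 and 0.98^55 = 0.329, and the saturation terms are negligible. So 1 − 0.432 × 0.671 = 0.71.

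| Assumed rate, both arms | P(placebo arm empty) | P(not finite), 55/28 | P(not finite), 50/25 |
|---|---|---|---|
| 1% | 76% | 90% | 91% |
| 2% | 57% | 71% | 75% |
| 3% | 43% | 53% | 58% |
| 5% | 24% | 28% | 33% |
| 10% | 5.2% | 5.5% | 7.7% |
| 20% | 0.2% | 0.2% | 0.4% |
| 30% to 70% | about 0 | about 0 | about 0 |

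The formula is symmetric, so the figures mirror at high rates, where the failure is an arm with everyone affected: 5.5% at 90%, 28% at 95% and 71% at 98% (55/28). The probability reaches 50% at a rate of about 3.2% and drops below 10% above about 8.2%.

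Unequal assumed rates (placebo/baricitinib, 55/28): 59% at 2%/5%, 24% at 5%/10% and 5% at 10%/20%. Adding covariates can make separation more likely but not less.

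**Illustration: 3/55 versus 0/28.**
- Ordinary logistic regression does not converge. The reported coefficient is about 24.5 with a standard error of about 168,000.
- Fisher's exact test gives p = 0.55.
- The Firth estimate, which in this 2×2 case equals adding 0.5 to each cell, is (3.5/52.5)/(0.5/28.5) = 3.8. Its log standard error is √(1/3.5 + 1/52.5 + 1/0.5 + 1/28.5) = 1.53, so the Wald 95% interval is 0.19 to 76.
- The exact 95% upper limit for 0/28 is 1 − 0.025^(1/28) = 12.3%.
- The observed risk difference is 3/55 − 0/28 = 5.5 percentage points, which is defined despite the empty cell.

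**The case against.** The other side has four good arguments.

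1. *Logistic regression is not the only comparative method.* Whether a participant had an AE is a categorical secondary outcome, so the general sentence on Fisher's exact test covers it, and that test is valid with empty cells. This stands, so a reader should not infer that the plan has no working comparison. But Fisher's test gives a p-value without an effect size or interval, and the AE sentence does not defer to it.

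2. *Failure is conditional.* A reader might infer that the model will often fail. The article gives no rates, so that is not established. The problem is confined to rates below about 5% or above about 95% and is nearly absent from 20% to 80%.

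3. *The endpoint can be read as a proportion.* It is tempting to say that logistic regression cannot measure AE frequency. The article does not define frequency as events per unit of time, and the proportion of participants affected is an ordinary meaning that fits the logistic sentence. Tables of incidence and grading of severity are also foreseen, although the tables are described under the interim heading. The supportable statement is that a yes/no model uses part of the endpoint. How much power is lost by ignoring repeat events depends on assumed rates and between-participant variation that the article does not give, so no figure is offered.

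4. *This is detail for the analysis plan, and the stakes are modest.* Firth and exact versions are still logistic regression, so the sentence is not contradicted, and the unseen analysis plan may specify one. In the 3/55 versus 0/28 example the Firth interval is so wide that the conclusion would not change. This limits the point to a minor one. It does not remove it, because the article names a method that, in its ordinary form, can return nothing usable for sparse events.

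**Conclusion.** The point holds in a limited form. At 55 versus 28, ordinary logistic regression has a substantial chance of giving no finite odds ratio for uncommon events: about 71%, 53% and 28% at assumed common rates of 2%, 3% and 5%, falling to 5.5% at 10%. The arithmetic is exact given the rates, but the rates are assumptions, and it takes treatment as the only covariate and independence between participants. For having any AE, the problem arises only if about 95% or more of participants are affected. Repeat events are not used, so the model covers the AE endpoint in part.

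The documents do not support the view that the safety analysis as a whole fails, since Fisher's exact test and descriptive tables remain. What is missing is a stated effect estimate with an interval that survives an empty cell. This is a minor improvement, not a flaw that threatens the trial's conclusions.

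**What to change.** Amend the AE sentence in section {20a} as follows:

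- For participants with at least one AE, at least one SAE, and each event type compared: counts by arm and the risk difference with a score (Miettinen-Nurminen) 95% confidence interval, alongside the Fisher's exact test already stated.
- If an odds ratio is wanted: Firth-penalised or exact logistic regression.
- For frequency: also events per participant-year by arm, with a rate ratio from a negative binomial model or a Poisson model with robust standard errors.

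Showing the 48 weeks on study drug and the 48 weeks afterwards separately would be a useful but optional addition.

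The cost is a change of wording and a few lines of code, with no new data. The downside is slightly more analysis work, and the plain odds ratio would no longer be the main safety summary.
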